### Blood cultures

Blood cultures were collected at QECH under standard protocol as described by (
Wilson
*et al.*, 2020)

### Statistics and analysis

**
*Description of statistical methods*
**

Data analysis will be carried out using the R environment for statistical computation
^
20
^. We will use changes in SBA along with OAg IgG as the primary measures of immunity in a modelling framework we have already developed, that combines censored regression with linear or cubic splines and allows principled change point analysis
^
21,
22
^ to identify the age of antibody and SBA nadir for each serovar. We will use this model to describe the impact of age, malaria exposure (MRDT), malnutrition, anaemia and eNTS exposure on SBA and OAg IgG. The models we develop will account for correlations between the paired samples using generalised estimating equations. Regression coefficients and confidence intervals will be calculated for each of the risk factors; malaria RDT positivity, MUAC, haemoglobin, and adjusted for season, poverty and sanitation. Percentage change in IgG and SBA between paired samples will be calculated, plotted against age and compared by season, using generalised linear models. Number of seroconversions by age will be calculated, with the seroconversion defined by fold-increases in IgG or SBA. The sero-incidence rates will be compared across risk factor groups and by season. Finally, additional contrasting datasets (cross-sectional sample sets from vacciNTS sites in Burkina Faso, Ghana and Kenya) will allow us to compare immunological markers in different settings.

As an exploratory analysis, mechanistic mathematical models will be developed to identify a population correlate of protection using acquisition of IgG and SBA by age with rates of invasive NTS disease by age. Additional exploratory analyses will include impact of RTS,S malaria vaccination on the development of immune response to NTS, graphical models (Bayesian networks, structural equation models or Gaussian copula graphical models), to interrogate the complex relationships between the immunological and environmental variables; and geospatial analyses of the GPS-mapped subject and household data.

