## Methods

### Study design

**
*Prospective community cohort*
**

We will carry out a prospective cohort study with paired serology samples at baseline and 3-months taken from the same individuals. Two thousand children aged 0–5 years sampled across age-strata will be recruited, randomly sampled throughout household-censused enumeration areas. We will spread sampling evenly throughout the year in Chikwawa district, Malawi, aiming to capture peak iNTS season in the middle of the study period. These children will be evenly recruited from the vaccinated (Montfort) and non-vaccinated clusters (Chikwawa) of the EPI-MAL trial. We will select households containing children 0–5 years via a two-stage sampling technique. In the first stage enumeration areas (EA) will be selected using probability proportional to size (PPS) sampling, with stratification according to malaria prevalence. In the second stage households containing children 0–5 years will be randomly sampled from selected Enumeration Area (EA). Any child eligible in the household will be invited to participate in the study.

We will collect approximately 2500 stool samples and 4000 paired blood samples (to account for 20% loss to follow-up), measuring antibody titres (IgG) and changes in serum bactericidal activity (SBA) for the most common NTS serovars (S. Typhimurium and S. Enteritidis) and other serovars, to understand the age-stratified acquisition of immunity and how this varies with risk factor exposure. We will perform anthropometric measurements, malaria (rapid diagnostic tests [RDT] and thick blood films), haemocue and sickle RDT to assess the association with the main risk factors. Any children found to have positive malaria tests will be provided treatment by the field team. Any child with a low haemoglobin will provided treatment according to the Integrated Management of Childhood Illnesses (IMCI)/ World Health Organisation (WHO) guidelines for management of anaemia
^
17
^ and referred to hospital for follow-up. A comprehensive record of the treatments administered throughout the study will be documented for subsequent analysis. Any child diagnosed with sickle cell disease or malnutrition (based on weight-for-height z-scores or Mid-Upper Arm Circumference (MUAC)) will be referred to the local health facility for further management.

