**Table 2. T2:** Detailed schema of SAiNTS field illustrating teams 3-monthly rotations through sequential enumeration clusters.

		**Q1, 2021**								**Q2, 2021**								** Q3, 2021**								**Q4, 2021**								**Q1, 2022**									**Q2, 2022**			
		**V1 C1**									**V2 C1**									**V2 C2**									**V2 C3**									**V2 C4**								
											**V1 C2**									**V1 C3**									**V1 C4**																	
**RTS,S unvaccinated**	1																																													
High malaria	2																																													
prevalence	3																																													
(Chikwawa)	4																																													
N=1200	5																																													
	6																																													
	7																																													
	8																																													
	9																																													
**RTS,S vaccinated**	10																																													
Low malaria	11																																													
prevalence	12																																													
(St Montfort)	13																																													
N=1200	14																																													
	15																																													
	16																																													
	17																																													
	18																																													

Scheme showing sampling rotation through enumeration areas (EAs) (1 to 18), with four cohorts (C1 to C4) starting at 3 monthly time intervals in each of the high and low malaria transmission areas. Each EA will be visited at four time periods throughout the year, to capture variations in seasonality. A total of 2400 children will be recruited, 1200 at each site, with 30-40 children recruited over 7-12 days at each EA at each round of recruitment. Each child will have paired samples collected 3 months apart, and the next cohort of children will be recruited at the same time as the day 90 follow-up at each EA.

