### Sample size

 All code can be found
here (
*Extended data*
^
18
^).

**
*Sample size simulations for serosurvey*
**

Simulated data (100,000 simulations) demonstrate an acceptable margin of error and confidence interval for estimation across all seroprevalences for 1000 single samples (200 in each of five age groups, from 0–11, 12–23, 24–35, 36–47, 48–60 months), as a minimum sample size for each site in Malawi, Kenya, Burkina Faso, and Ghana (
Figure 5).

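### The analysis section accounts for correlation only within a child's pair of samples, although children come as whole households from 18 enumeration areas; intervals for seroprevalence, seroincidence and area- or household-level factors are likely to be too narrow

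*Protocol article*

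**What the plan says.** Sampling (Study design). The first stage reads: "In the first stage enumeration areas (EA) will be selected using probability proportional to size (PPS) sampling, with stratification according to malaria prevalence". Households with children aged 0–5 years are then drawn at random within each selected EA, and no further selection takes place: "Any child eligible in the household will be invited to participate in the study". The footnote to Table 2 gives 18 EAs, nine per area, and adds: "Each EA will be visited at four time periods throughout the year, to capture variations in seasonality". It sets the numbers as follows: "A total of 2400 children will be recruited, 1200 at each site, with 30-40 children recruited over 7-12 days at each EA".

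Analysis (Statistics and analysis). The only statement on dependence is: "The models we develop will account for correlations between the paired samples using generalised estimating equations". Percentage change between samples is to be analysed with generalised linear models, and sero-incidence is to be compared across risk-factor groups and seasons; neither sentence mentions correlation. Risk-factor coefficients are adjusted for season, poverty and sanitation. Mapped household location is used only in an exploratory geospatial analysis.

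Sample size. The serosurvey simulations are said to "demonstrate an acceptable margin of error and confidence interval for estimation across all seroprevalences for 1000 single samples", that is, 200 in each of five age groups. Neither this text nor the power text mentions a design effect.

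**The concern.** Correlation within a child's pair of samples is the least of the dependence in this design. Baseline seroprevalence uses one sample per child, and percentage change and seroconversion reduce each pair to one record. For these outputs (objectives 1 and 2) a pair-level GEE changes nothing, and children are in effect treated as independent.

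The protocol's own framework (Model of exposure and immunity) says that immunity to NTS is shaped by poverty, sanitation, season, malaria and malnutrition. Poverty and sanitation are measured by a household wealth and WASH questionnaire, and the EAs are stratified by malaria prevalence. Positive correlation between children of the same EA or household is therefore what the protocol leads one to expect.

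At stake is the stated precision of the age-specific estimates meant to identify windows of susceptibility and inform vaccine strategy, and the error rate of comparisons of factors that differ mainly between EAs or households.

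**Working it through.** **Inputs from the article.** 18 EAs; 2400 children (Table 2 footnote) or 2500 (Sample size); five age bands; 20% loss to follow-up; for the enteric NTS (eNTS) power, SBA difference 0.2, SD 0.4, prevalence 8%. **Assumed, not in the documents:** ICC 0.01 to 0.05, and two-sided 5% for the power.

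**1. The plan's own figure.** 2500 × 0.8 = 2000 children, 160 exposed and 1840 not. SE = 0.4 × √(1/160 + 1/1840) = 0.0330, and 0.2/0.0330 = 6.07. Power = Φ(6.07 − 1.96) = 99.998%, against 99.97% stated; with 1600 pairs (128 and 1472) it is 99.97%. The stated power is thus what independent children give, with no clustering term.

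**2. Age-specific seroprevalence.** Children per EA per band: m = (2500/5)/18 = 27.8 (26.7 with 2400). Design effect = 1 + (m − 1) × ICC; actual coverage of a nominal 95% interval = 2Φ(1.96/√design effect) − 1.

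| ICC | Design effect | Coverage |
|---|---|---|
| 0.01 | 1.27 | 91.8% |
| 0.02 | 1.54 | 88.6% |
| 0.05 | 2.34 | 80.0% |

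For seroincidence, with 2000 followed children, m = 400/18 = 22.2; the design effect is 1.21 to 2.06 and coverage about 92% to 83%.

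**3. EA-level or site-level factors, all ages.** m = 2400/18 = 133.3; the design effect is 2.32, 3.65 and 7.62 at ICC 0.01, 0.02 and 0.05. Even at a design effect of 2, a 5% test has type I error 2[1 − Φ(1.96/√2)] = 16.6%.

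**4. Child-level risk factors.** The inflation is about 1 + (m − 1) × ICC_y × ICC_x, where the two ICCs are those of outcome and risk factor. With both at 0.05: 1 + 132.3 × 0.0025 = 1.33, giving type I error 2[1 − Φ(1.96/√1.33)] ≈ 9%. With ICC_x = 0 it is exactly 1.

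A simulation (18 EAs of 111 children, outcome ICC 0.05, 1000 runs) agrees. Intervals clustered on the child covered 95%, 93% and 86% for a risk-factor coefficient as the SD of the EA log-odds of the risk factor rose from 0 to 0.5 to 1.0. Intervals clustered on the EA covered about 95% in all three.

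**5. Household level.** With an assumed 1.5 to 2 children per household and household ICC 0.1 to 0.3, the design effect is 1 + 0.5 × 0.1 = 1.05 to 1 + 1 × 0.3 = 1.30. The EA level dominates.

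**6. Does the planned size survive?** Effective number per age band: 500/1.27 = 394 to 500/2.34 = 214, still above the 200 used for the margin of error. At 50% seroprevalence the margin is 1.96 × √(0.25/500) = 4.4 points if children are independent, 4.9 to 6.7 points with the design effect, and 6.9 points for 200 independent children. For the eNTS power, applying the full design effect (m = 2000/18 = 111; a worst case for a child-level exposure) gives 98.7%, 92.4% and 66.2% at ICC 0.01, 0.02 and 0.05.

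**The case against.** The strongest reply is that the article condenses a fuller protocol, with code held elsewhere. The GEE sentence does not say that only paired samples are handled, and it does not define the cluster identifier; variance estimators and design effects are often left to the full document. This stands in part. But the sentence does name the level of correlation, and an analyst who follows it would cluster on the child. That is a choice stated too narrowly, not just detail left out.

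Other mitigating features also stand in part. Within-child change removes stable EA and household differences, so its ICC may be lower than that of antibody levels. Adjusting for season, poverty and sanitation, and accounting for the malaria stratum, would lower the residual ICC. Four rounds per EA may dilute clustering tied to one time. None of these makes the ICC zero, and unadjusted age-specific seroprevalence benefits least.

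Three stronger readings are tempting, and the documents do not support them:

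- A reader might apply the 16.6% type I error, with 80% power falling to about 51%, to malaria. Those figures belong to a design effect of 2 for an EA- or site-level contrast. Malaria is analysed as each child's rapid-test result, so the product formula in step 4 applies. The RTS,S comparison, which is closest to a site contrast, is expressly exploratory.
- A reader might conclude that the sample size is inadequate. Step 6 shows that the planned Malawi numbers absorb the assumed design effect for the age-band margins, and that the eNTS power has headroom at ICC 0.02 or below.
- A reader might infer that equal recruitment from two areas biases the district estimate because no weights are mentioned. The article does not say that unweighted pooling will be used, and weighting is commonly left to the full protocol.

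**Conclusion.** The point holds as a should-fix. As written, the analysis ignores dependence between children of the same EA and household, and the GLM and sero-incidence analyses name no correlation at all. If the ICC is positive, reported precision will be overstated for age-specific seroprevalence and seroincidence, and for EA-, household- or site-level factors. The loss is modest at ICC 0.01 (about 92% coverage for an age band) and material at 0.05 (about 80%). Child-level risk-factor coefficients are affected less, and those for factors varying only within EAs not at all.

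All sizes rest on an assumed ICC, equal cluster sizes and a normal reference. The article gives recruitment totals of 2000, 2400 and 2500 in different places; this shifts the cluster size slightly and leaves the conclusion unchanged.

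**What to change.** - State that the EA is the independent cluster in the GEE, GLM, seroprevalence and sero-incidence analyses, with a small-sample-corrected robust variance (for example Kauermann-Carroll or Mancl-DeRouen) and a t reference, because there are only 18 clusters. Alternatively, fit random intercepts for EA, household and child, which suits the censored-regression framework.
- Include the malaria stratum as a covariate. In Table 2 the stratum coincides with the RTS,S area, so it cannot be separated from a comparison of the two areas; EA clustering does not resolve that confounding.
- State that the sample size figures assume independent children, or quote them again over a range of design effects.

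Cost: a sentence or two in the analysis section and a re-run of the margins. EAs and households are mapped and censused, so no new data and no change to sampling are needed. The downside is wider intervals. An EA-robust variance does not require the ICC to be known in advance.

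### The stated risk-factor regression leaves out the high/low malaria area stratum, so the malaria RDT coefficient takes up part of any other difference in immunity between the two areas

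*Protocol article*

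**What the plan says.** Sampling (Study design, Prospective community cohort). "In the first stage enumeration areas (EA) will be selected using probability proportional to size (PPS) sampling, with stratification according to malaria prevalence". Recruitment is balanced across the two areas: "These children will be evenly recruited from the vaccinated (Montfort) and non-vaccinated clusters (Chikwawa) of the EPI-MAL trial". Table 2 ties the two features together. Enumeration areas 1 to 9 are Chikwawa, high prevalence and RTS,S unvaccinated; 10 to 18 are St Montfort, low prevalence and RTS,S vaccinated; 1200 children come from each. The rotation runs "four cohorts (C1 to C4) starting at 3 monthly time intervals in each of the high and low malaria transmission areas", so every enumeration area is visited in all four periods.

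Analysis (Statistics and analysis). The purpose of the model is given as follows: "We will use this model to describe the impact of age, malaria exposure (MRDT), malnutrition, anaemia and eNTS exposure on SBA and OAg IgG". Correlation is handled within the child only: "The models we develop will account for correlations between the paired samples using generalised estimating equations". The adjustment set for the risk-factor coefficients is then given: "Regression coefficients and confidence intervals will be calculated for each of the risk factors; malaria RDT positivity, MUAC, haemoglobin, and adjusted for season, poverty and"; the list closes with sanitation. Neither area, enumeration area nor RTS,S status is named for this model. The RTS,S comparison and the geospatial work are separate exploratory analyses. The matching described under Study design serves the vaccinated versus unvaccinated comparison only.

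**The concern.** Because the strata are defined by malaria prevalence, a child with a positive RDT is more likely to come from Chikwawa than a child with a negative one. If the two areas also differ in immunity for reasons other than the child's own malaria (local Salmonella circulation, access to care, any vaccine effect by another route), a model without area attributes part of that difference to malaria.

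The stated covariates do not close the gap. Season is balanced across areas by the rotation. Poverty and sanitation may explain some of an area difference, but they do not stand for the stratum. The generalised estimating equations address correlation within a child, and robust standard errors, by child or by enumeration area, leave the bias in the coefficient. The coefficients for MUAC and haemoglobin are exposed in the same way if those measures differ by area.

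At stake is specific objective 3: an area difference could be reported as a malaria effect, or could mask one.

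**Working it through.** **The plan's own figures.** No printed figure is disputed; they serve to set the scale.
- The eNTS power calculation (difference 0.2, SD 0.4, 8% prevalence, 2,500 recruited, 20% loss; two-sided 5% level assumed) has groups of 160 and 1,840. SE = 0.4 × √(1/160 + 1/1840) = 0.033, and power is 99.998%, close to the stated 99.97%.
- The malaria row of Table 4 (0.25, 16%, N = 2,500, at least 80% power) has no stated SD. As a simple two-group comparison, exactly 80% power implies SD = 0.25 / 2.80 / √(1/400 + 1/2100) = 1.64. The anaemia, malnutrition and sickle cell rows give 1.61, 1.62 and 1.60 in the same way. An SD of 1.6 is therefore assumed below; the only SD that the article states for SBA is 0.4.

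**Share of an area difference D carried by the RDT coefficient, level outcome, working independence.** With equal allocation and area prevalences ph and pl averaging 16%:

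share = 0.25 × (ph − pl) / (0.16 × 0.84)

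| Assumed split | Share | SE increase when area is added |
|---|---|---|
| 16%/16% | 0 | 0% |
| 20%/12% | 0.149 | 0.6% |
| 24%/8% | 0.298 | 2.5% |
| 28%/4% | 0.446 | 5.8% |

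The SE increase is √[0.1344 / w], where 0.1344 = 0.16 × 0.84 and w is the mean of ph(1 − ph) and pl(1 − pl). A least-squares simulation at 24%/8% with D = 1 and no malaria effect gave 0.295 without area and 0.000 with it.

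**Exchangeable working correlation ρ = 0.5.** Assume that RDT results at the two visits are independent given area. The area gap then enters only through the sum of the two visits, while the within-child contrast is free of it. With b = 0.25(ph − pl)²:

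share = [(ph − pl)/3] / [(2w + 4b)/3 + 2w]

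This gives 0.075, 0.152 and 0.236 for the three unequal splits, about half the figures above. If RDT status persisted between visits, the share would move back towards them.

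**Illustration only.** Assumed: 24%/8% split, SD 1.6, D = 0.32 (0.2 SD), 2,000 children with two visits, within-child correlation 0.5, no malaria effect.
- Level, independence: bias 0.298 × 0.32 = 0.095, SE 0.070, false-positive rate 28% by formula and 26% to 27% in simulation.
- Level, exchangeable: bias 0.152 × 0.32 = 0.049, SE 0.060, rate 13% by formula and 12% in simulation.
- Level, area added: about 5%.
- Paired change regressed on baseline RDT: the constant gap cancels, and the rate is about 5%.
- Paired change when one area gains 0.15 more over three months: bias 0.298 × 0.15 = 0.045, SE 0.098, rate about 7%. For scale, the article equates 0.25 with 2.5 months of natural gain, so three months is about 0.25 × 3/2.5 = 0.30, and 0.15 is half of that.

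With a true malaria effect of −0.25, level outcome and independence, the estimate shrinks to −0.25 + 0.095 = −0.155. Power falls from about 94% to 95% with area in the model to about 60% to 64% without it.

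**The case against.** **The change outcome.** The article names changes in SBA among its primary measures and powers malaria on a change between samples, and there a constant area gap cancels. This stands, and it limits the point mainly to the level models. Those are still planned, since the model describes effects on SBA and IgG themselves, and a different rate of acquisition would still bias a change.

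**The inputs.** The prevalence split, the area gap and the SD of 1.6 are not in the article, and nothing in it shows that immunity differs between the areas. This also stands. At the stated SD of 0.4, a 0.2 SD gap is 0.08 and the bias is 0.298 × 0.08 = 0.024, about a tenth of the 0.25 target. The false-positive rate depends on the gap in SD units, so it would not change for the same 0.2 SD gap. The power illustration does depend on the SD.

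**RTS,S.** A reader might infer that the malaria coefficient absorbs the whole Chikwawa–Montfort difference, vaccine effect included. The article does not support that. Only a share is absorbed. The stated rationale is that the vaccine may act because malaria impairs bactericidal activity, and an effect through the child's own malaria belongs to the malaria effect. Table 4 assumes 60% coverage, so area is not individual vaccine status.

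**The estimand.** RDT stands for current or recent malaria, and conditioning on area removes long-term exposure, which may be of interest under an exploratory objective. This is a reason to report both models, not to omit area.

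**Condensed article.** The covariate sentence may not be exhaustive: age and eNTS appear only in the sentence on the model. But the text does state an adjustment set, and the stratum on which the sample is built is absent from it.

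**Conclusion.** The point holds as a cheap improvement to a stated model. Without the area stratum, the malaria RDT coefficient in level models takes about 15% to 45% of any area difference that does not act through the child's own malaria. This assumes working independence and splits of 20%/12% to 28%/4%. The share is about 7% to 24% under an exchangeable working correlation of 0.5 with RDT independent between visits given area. It is zero if prevalence is the same in both areas, and smaller where poverty and sanitation explain part of the difference. For paired changes only a difference in the rate of acquisition matters, and its effect is likely small.

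A reader might take the false-positive rate of about 26%, or the fall in power from about 95% to 64%, as the expected performance of the plan. The article does not support that: both need a level outcome, working independence, an SD of 1.6 and an area gap of 0.32, none of which it fixes together.

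**What to change.** In Statistics and analysis, add the area stratum (Chikwawa or Montfort), or enumeration-area fixed effects, to season, poverty and sanitation for each risk-factor coefficient. Do this in the IgG and SBA level models and in the change models. Report the model without area beside it, labelled as including between-area differences such as long-term malaria intensity.

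Area is already known for every child, so no new data are needed. The standard error of the malaria coefficient rises by about 1% to 6% over the assumed splits. The area-adjusted coefficient excludes the effect of area-level cumulative malaria exposure, which is why the second model should be kept.

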**The acquisition of natural systemic immunity**

We have described the age-stratified sequential acquisition of CD4 cellular immunity, followed by functional antibody-mediated immunity and serum bactericidal activity (SBA) against iNTS among children in Malawi
^
11
^. This demonstrated the nadir of functional humoral immunity, which occurs after the waning of maternal antibody, but before the sequential acquisition of first cellular immunity, then anti-LPS IgG antibody and associated functional SBA. This nadir coincides with the peak incidence of iNTS disease among children at nine-13 months, further demonstrating how a serological protective threshold of humoral protection develops following eNTS exposure over time.

Robust defence against iNTS requires both cellular and humoral immunity, and we have previously demonstrated both cellular and humoral defects that cause susceptibility to iNTS disease. Humoral and cellular defences have both been shown to be impaired in current and recent uncomplicated malaria
^
16
^. Bound, complement-opsonised antibody is required both for SBA, and for uptake of bacteria by phagocytes prior to killing by respiratory burst.

There are critical current knowledge gaps in our understanding of the relationship of enteric Salmonella exposure and the development of protective immunity amongst those in the highest risk age bands; of what are the correlates of protection for iNTS disease; and of how the effect of known susceptibility risk factors in different populations affect these relationships.

Several mechanisms of humoral and cellular immunity are required for protection against iNTS disease, and different risk factors act on different elements of the immune response. This means that some of the resultant background immunological susceptibilities might be fully vaccine-responsive (e.g. a lack of sufficient protective antibody), while others might not be fully ameliorated by vaccine-induced immunity (e.g. periods of complement deficiency, or failure of respiratory burst due to haemosiderin damage to phagocytes). This means that the potential impact of vaccine deployment to prevent iNTS disease might be different in different epidemiological settings.

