### Objectives

**
*Broad objective*
**

To understand the acquisition of immunity to NTS and epidemiology of eNTS in children 0–5 years, and how this immunity varies with risk factors (malaria, anaemia, malnutrition and sickle cell disease) and geographical setting.

**
*Specific objectives*
**

1.   To estimate the seroprevalence by age of NTS in children 0–5 years in Chikwawa, Malawi.

2.   To estimate the seroincidence by age of NTS in children 0–5 years in Chikwawa, Malawi.

3.   To explore the effect of the main risk factors: malaria, malnutrition, anaemia, and sickle cell disease on the acquisition of humoral immunity to NTS (IgG and SBA).

4.   To describe the relationship between IgG and SBA including effect modification by age.

5.   To estimate the age-stratified seroprevalence of Salmonella enteric infections (eNTS) by risk factor group: malaria, malnutrition, anaemia, and sickle cell disease.

6.   To compare age-stratified acquisition of immunity to NTS across sub-Saharan African settings (Vacci-NTS sites: Kenya, Malawi, Burkina Faso, Ghana).

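### Two paired-sample summaries are ratios to the visit 1 value: mean percentage change is positive when nothing changes, and fold-rise seroconversion under-detects infection in infants whose visit 1 titre is still largely maternal

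*Protocol article*

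**What the plan says.** The Study design section describes a "prospective cohort study with paired serology samples at baseline and 3-months taken from the same individuals". From those pairs, the Statistics and analysis section derives two summaries of change:

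- Percentage change: "Percentage change in IgG and SBA between paired samples will be calculated, plotted against age and compared by season, using generalised linear models".
- Seroconversion: "Number of seroconversions by age will be calculated, with the seroconversion defined by fold-increases in IgG or SBA". The counts are then used as rates: "The sero-incidence rates will be compared across risk factor groups and by season".

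The second summary serves specific objective 2: "To estimate the seroincidence by age of NTS in children 0–5 years in Chikwawa, Malawi".

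Three other parts of the article bear on the point.

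- Children enter from birth. The Sample size section for the serosurvey plans "200 in each of five age groups, from 0–11, 12–23, 24–35, 36–47, 48–60 months".
- The section on immunological susceptibility attributes protection before six months to breastfeeding and maternal antibody. The section on acquisition of natural systemic immunity says of earlier work: "This demonstrated the nadir of functional humoral immunity, which occurs after the waning of maternal antibody". It places that nadir with peak disease at nine to 13 months.
- The main model of IgG and SBA is a separate analysis. It is a censored regression with splines and change-point analysis, with generalised estimating equations for the pairing, and it is not stated to use a ratio.

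**The concern.** Both summaries divide by a single visit 1 measurement, and each division causes its own problem.

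**Percentage change.** The scale is asymmetric: a halving is −50% and a doubling is +100%. Generalised linear models target an arithmetic mean, and the mean ratio of two noisy titres exceeds 1 when nothing has changed. A log link does not help, because it still models the mean of the ratio. The measure is also unstable when visit 1 is low, and arbitrary when visit 1 is below the detection limit. The plan already allows for censoring in its main model, but not in this summary.

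**Fold-rise seroconversion.** In a young infant the maternal part of the visit 1 titre falls passively over three months. An infection must first make up that fall before any rise over visit 1 can show. The same rise criterion is therefore less sensitive in these infants than in older children, although the count is reported by age. Comparisons across risk groups would be affected too if the groups differ in their share of young infants.

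**Working it through.** **Inputs from the article:** interval of three months (90 days used); enrolment from birth; maternal antibody present before six months and then waning. The article gives no figure for either summary, so there is none to reproduce. It gives no maternal half-life, fold cut-off, response size or within-child variability on a log scale. All of these are assumed below.

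**1. Percentage change with no true change**

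Let the log10 ratio of visit 2 to visit 1 be normal with mean 0 and SD s. Then mean percentage change = exp((s × ln 10)² / 2) − 1.

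| s (log10 ratio) | (s × 2.3026)² / 2 | Mean percentage change | Geometric mean change |
|---|---|---|---|
| 0.2 | 0.106 | +11% | 0% |
| 0.4 | 0.424 | +53% | 0% |
| 0.5 | 0.663 | +94% | 0% |

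A simulation of 400,000 pairs matched the equivalent formula for per-visit SDs. The median and the back-transformed mean log change stayed at zero, within about 0.1%.

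A case that needs no distribution: half the children double and half halve. The mean percentage change is (100 − 50)/2 = +25%; the mean log change is zero.

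Season contrast: if s is the same in two seasons, the inflation is the same in both and cancels in the difference. If s is 0.2 in one and 0.4 in the other, the false difference is 53 − 11 = 42 percentage points.

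**2. Fold-rise seroconversion with maternal decay**

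Assume infection multiplies the titre expected at visit 2 by a lognormal factor with median 8 and log10 SD 0.35. With half-life h, the passive fall is D = 2^(90/h). The probability of meeting a cut-off c is 1 − Φ((log10 c − log10 8 + log10 D) / 0.35).

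| Half-life (days) | D | 2-fold rule | 4-fold rule |
|---|---|---|---|
| No maternal antibody | 1 | 96% | 80% |
| 90 | 2.0 | 80% | 50% |
| 60 | 2.8 | 67% | 33% |
| 45 | 4.0 | 50% | 20% |
| 30 | 8.0 | 20% | 4% |

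Worked line, 2-fold rule, 45 days: (0.301 − 0.903 + 0.602)/0.35 = 0, giving 50%.

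The median response is itself assumed. Under the 2-fold rule:

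- Median 4-fold: 80% without maternal antibody, against 20% (45 days) and 4% (30 days).
- Median 16-fold: 99.5%, against 80% and 50%.

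A simulation with different assumptions (median 8-fold, natural-log SD 0.8, assay natural-log SD 0.2 per visit, half-lives 28 to 60 days) gave 95% falling to 16–66% for a 2-fold rule and 79% falling to 3.5–34% for a 4-fold rule.

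Finally, suppose the response adds to the remaining titre instead of multiplying it. With a non-maternal baseline of 0.5 units, a maternal titre of 5 units at visit 1 and a median own response of 8 units, 4-fold sensitivity falls from 97% with no maternal antibody to 13–14% (half-lives 28 and 42 days).

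**3. Who is affected**

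Visit 1 before about six months covers 6/12, or half, of the 0–11 month stratum if ages are even. If infections also fell evenly, and all of those infants had the 45- or 30-day loss, stratum sensitivity under the 2-fold rule would be (0.957 + 0.500)/2 = 73% or (0.957 + 0.195)/2 = 58%, against 96% in older strata.

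**The case against.** **Detail may sit elsewhere.** The article condenses a longer protocol. A fold cut-off, an infant rule, detection-limit handling and the model scale may be in documents not shown. This stands for the missing cut-off, which is not counted as a fault. It does not remove the point, because the article does state percentage change and fold-increase as the measures. That the percentage change is summarised by its mean is inferred from the generalised linear model; a median or log-ratio analysis would avoid the inflation, but none is stated.

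**The susceptibility window.** A reader might infer that the fold rule biases incidence downward in the window that the study wants to locate. The article does not support that. It places the nadir and peak disease at nine to 13 months, after maternal antibody has waned, and assigns the age of the nadir to the spline and change-point model, which uses no fold rule.

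**Other plans.** Exploratory objective 4 uses antibody kinetics to inform seroincidence, and a longitudinal subset is bled at six, nine and 12 months to follow waning. Both are relevant, but neither mentions maternal antibody or changes the stated seroconversion rule.

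**Season contrasts.** A reader might infer that these are invalid. They are not if within-child variability is similar across seasons, and the article gives no evidence that it differs. Table 2 also has each enumeration area visited in four periods of the year. What remains is an inflated level against age, and a contrast exposed to any difference in variability.

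**Size.** Every magnitude rests on assumed inputs. This stands; only the directions follow from the article itself.

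**Conclusion.** The point holds in a limited form.

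- **Percentage change.** Its mean is inflated under no change, by about 11% to 94% for assumed log10-ratio SDs of 0.2 to 0.5. This affects the level plotted against age, and affects season contrasts only where variability differs.
- **Seroconversion.** Sensitivity is reduced in infants whose visit 1 titre is still largely maternal, so seroincidence by age is too low in the youngest part of the 0–11 month stratum. The direction requires only that maternal antibody declines between visits. The size depends on half-life, response and cut-off. The loss is partial: infections with a large enough response are still detected.
- **Not affected.** The main censored spline model, the age of the nadir, and the sample size.

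This should be corrected before analysis. It bears on a named objective, and a better method is already within the planned framework.

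**What to change.** 1. Replace percentage change with log10(visit 2) minus log10(visit 1), analysed within the planned censored-regression framework so that values below detection at either visit are handled. Report geometric mean fold change by age and season.
2. Keep young infants (mainly visit 1 before about six months) in the seroincidence results, but as a separate stratum flagged as a lower bound. Show the risk-group and season comparisons with and without them. Dropping them altogether would not serve objective 2, which covers 0–5 years.
3. As a sensitivity analysis, define seroconversion in these infants against the expected decayed visit 1 titre, over a range of decay rates. A rate fitted to eNTS-negative infants may be too slow: the longitudinal subset section anticipates missed exposures between visits, and the introduction reports 8–9% stool positivity in any month in an earlier cohort. Undetected boosting would make decay look slower than it is.

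Cost: no new data, slightly more analysis, and less precise incidence in the youngest infants.
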